**Table 1 pone.0350169.t001:** Inclusion and Exclusion Criteria for the Extreme Visceral Pain and Lack of Visceral Pain cohorts. Comprehensive eligibility matrix for the remote mobile app sub-study, wearable sensor sub-study, and bio-sampling sub-study. Common criteria: ≥ 18 years, UK-based, informed consent capable. Sub-study exclusions ensure safety (pacemakers, contact dermatitis), feasibility (travel restrictions), and cohort purity (no confounding pain conditions). Criteria support n = 350 total recruitment with n = 100 wearable sub-study power (80% power).

Sub-study	Inclusion Criteria	Exclusion Criteria
Remote mobile app	Pain, or lack of pain, associated with one or more of the specified visceral diseases or chronic pain conditions as diagnosed by an expert NHS medical professional.	Not able to fulfil the inclusion criteria
	Able to provide informed consent electronically	
	Aged 18 years and over	
	Living in the UK	
Wearable sensor	Able to fulfil the inclusion criteria of the remote mobile app sub-study	Unable to attend or visit the research site.*
		Travel abroad in the plan duration of wearable sub-study
	Have completed and adhered to the procedure in remote mobile app sub-study	
		Unable or unwilling to use body sensor for any reason (e.g. contact dermatitis over wear zone, implanted pacemaker or defibrillator, allergy or hypersensitivity to nickel)
Bio-sampling	Pain associated with one or more of specified visceral diseases or pain condition diagnosis by an NHS medical professional	Unable to attend or visit the research site.*
	Meet further clinical criteria for genetic sampling and analysis (see Supplementary Information)	
	Able to provide informed consent	Not able to fulfil the inclusion criteria
	Aged 18 years and over	
	Lives in the UK	

** Participants are eligible for the study regardless of their location, as long as they are willing and able to travel to the research site.*

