### Bio-sampling

Participants from Extreme Visceral Pain and Lack of Visceral Pain cohorts will be asked to provide various samples to help researchers understand the similarities and differences in how conditions affect chronic visceral pain. Participants may choose to donate some samples while opting out of others, including those used in research involving non-human models.

**Whole blood:** Up to 50 mL of whole blood will be obtained through venepuncture. 5 mL of the whole blood sample will be sent for DNA extraction at the Department of Medical Genetics, University of Cambridge. 40 mL of the whole blood sample will be processed and sent for analysis and long-term storage to the Wolfson Sensory, Pain and Regeneration Centre at King’s College London. 5 mL of the whole blood sample will be processed and sent for long term storage to the Centre for Reproductive Health, Institute for Regeneration and Repair, University of Edinburgh.

**Urine:** Participants will collect mid-stream urine samples using a sterile device (UNI0054 or Colli-pee) at home or in the clinic, returning the samples via post. The urine sample will be sent to the Centre for Reproductive Health, Institute for Regeneration and Repair, University of Edinburgh.

**Vaginal swab:** Participants will self-collect a low vaginal swab (using BBLtm culture Swab MaxV or OMNIgene•vaginal | OMR-130), following provided instructions, and return the sample by post. The vaginal swab samples will be sent to the Centre for Reproductive Health, Institute for Regeneration and Repair, University of Edinburgh.

**Faeces:** Participants will collect up to three samples (using OMNIgene•GUT | OMR-200) at home and send them by post to the Cambridge Institute for Medical Research, University of Cambridge.

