### Key exploratory endpoint

The goal at the exploratory phase is to identify genetic variants that regulate visceral pain in people with visceral pain disorders, or in individuals who continue to experience pain despite remission or treatment. While we aim to conduct hypothesis-generating research, the genetic analysis will focus on identifying potential variants with moderate to strong effects, acknowledging that smaller effect sizes may require larger cohorts for reliable detection. The genetic approaches used have been proven effective in cohorts as small as 30–200 individuals with pain phenotypes [18]. However, we acknowledge that the requirement for ≥30 exomes per visceral disease pain phenotype may limit statistical power to detect genetic variants with modest effect sizes. Our analysis will explicitly report effect sizes, confidence intervals, and limitations related to sample size constraints in all genetic findings. Where modest effect sizes are detected, these will be flagged as requiring replication in larger cohorts. Findings will be reported in line with STREGA and STROBE guidelines for genetic association studies.

We note the following:

At least 30 exomes are required per visceral disease pain phenotype to yield statistically valid results, in terms of the power to detect significant associations between genetic variants and pain phenotypes.DNA extraction failure rates are expected to be no more than 5% from blood samples and negligible from serum samples.

For this study, the following visceral pain phenotypes will be analysed, representing a broad spectrum of pain associated with visceral organ pathology:

1Polycystic kidney disease2Inflammatory bowel disease3Post-vaginal mesh surgery4Chronic pancreatitis5Endometriosis6Painful bladder syndrome

Additionally, similar analyses will be conducted in the Lack of Visceral Pain cohort, where the severity of visceral disease does not correspond to expected levels of pain. This group will allow us to explore potential genetic mechanisms underlying discordant pain experiences. The following phenotypes will be included in this cohort:

1Polycystic kidney disease2Inflammatory bowel disease3Chronic pancreatitis4Chronic pain syndromes (e.g., fibromyalgia, Complex Regional Pain Syndrome, migraine)5Cases of painlessness during percutaneous visceral organ procedures (e.g., biopsies)6Overactive bladder syndrome

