This group will provide an exploratory dataset to investigate genetic variants that may regulate pain perception independent of disease severity.

**Mendelian gene effects** will be explored through multiple exome analyses, conducted in three steps:

1Candidate genes2Genes identified in ADVANTAGE pre-clinical research as important for visceral pain in rodents3Agnostic analysis to discover unknown genes associated with visceral pain

These methods, widely used in UK Clinical and Medical Genetics practice, will compare results to local, national, and international normative databases.

**Functional SNP allele discovery (fSNPd)** will be used to detect Single Nucleotide Polymorphisms (SNPs) that may cause a pain phenotype triggered by environmental factors [43]. The approach is based on three principles:

SNP alleles that cause fully penetrant effects are likely to be exonic and protein-changing (e.g., mis-sense, non-sense, indels, or splicing).Exome sequencing can detect most of these SNPs.Smaller cohorts are easier to collect, phenotype, and examine.

We will analyse exomes from multiple individuals to identify SNPs that occur at significantly different frequencies compared to the general population. Confounding variables will be minimized by matching subsets of control cohorts based on ethnicity or country. SNPs with significantly higher or lower allele frequencies in the study population will be identified through a two-tailed chi-squared test with Bonferroni and false discovery rate corrections applied.

Exome data will also be analysed for **mitochondrial genome variants** using methods developed in [name] laboratory at the MRC Mitochondrial Biology Unit. Any findings are expected to be mosaic. These results will be compared to established normative ranges for human mitochondrial variants.

Mitochondrial variants will be evaluated for **heteroplasmy levels** and potential **mosaic/somatic variants** using established bioinformatics pipelines and clinical reporting thresholds appropriate for the specific analysis platform and cohort characteristics. Variant calling and heteroplasmy quantification will follow current best practices as defined by relevant clinical genomics standards and validated reference databases. All mitochondrial variant findings will be interpreted in the context of established population frequency data and clinical significance guidelines current at the time of analysis.

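### The exome SNP scan compares patients who have both disease and pain with the general population, so alleles that only raise disease risk can be reported as pain alleles

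*Protocol article*

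**What the plan says.** **Aim.** Under Key exploratory endpoint the protocol states: "The goal at the exploratory phase is to identify genetic variants that regulate visceral pain in people with visceral pain disorders".

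**Comparator.** The same section says the scan will "identify SNPs that occur at significantly different frequencies compared to the general population". On confounding it says: "Confounding variables will be minimized by matching subsets of control cohorts based on ethnicity or country". The test is a "two-tailed chi-squared test with Bonferroni and false discovery rate corrections applied". The number of SNPs, the significance threshold and the size of the reference set are not given. The separate Mendelian analyses also use external references: they "will compare results to local, national, and international normative databases".

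**Phenotypes.** Six pain phenotypes are listed, each said to need at least 30 exomes. A second list of six applies to the Lack of Visceral Pain cohort, in which analyses of the same kind are planned. The lists share three diseases: polycystic kidney disease, inflammatory bowel disease and chronic pancreatitis. Post-mesh surgery, endometriosis and painful bladder syndrome have no same-disease entry in the Lack list.

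**Who gives samples.** The Bio-sampling section says: "Participants from Extreme Visceral Pain and Lack of Visceral Pain cohorts will be asked to provide various samples". The Fig 1 legend agrees and mentions blood for DNA. The bio-sampling row of Table 1 instead requires: "Pain associated with one or more of specified visceral diseases or pain condition diagnosis by an NHS medical professional". The app row of the same table admits patients with pain and patients without it.

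**The concern.** Cases and controls in this scan differ in two respects, disease and pain, and the analysis attributes any frequency difference to pain. Matching on ancestry deals with population stratification but not with disease. Bonferroni and false-discovery-rate corrections limit chance findings. Here the frequency difference is real and only its label is wrong, so correction leaves it in place. Replication against another general-population sample would reproduce the same error.

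The plan recognises the issue elsewhere: the autoantibody regressions under Secondary endpoint analyses adjust for disease type. No corresponding step is stated for the SNP scan, although the study intends to sample low-pain patients with three of the same diseases. At stake is whether a reported hit can be read as evidence about pain at all.

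**Working it through.** **The plan's own figure.** The minimum of 30 exomes per phenotype cannot be reproduced, because no allele frequency, effect size, threshold, power or SNP count accompanies it. What follows is an illustration on stated assumptions.

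**Inputs.** From the protocol: 30 exomes, that is 60 alleles, and a two-sided chi-squared test with Bonferroni correction. Assumed: 20,000 tests, so alpha = 0.05/20,000 = 2.5e-6; 20,000 reference alleles; and an allele that affects disease risk and not pain, with population frequency p0 and allelic odds ratio OR.

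**Step 1, frequency in cases.** p1 = OR·p0 / (1 − p0 + OR·p0). At p0 = 0.05:
- OR 2: 0.10/1.05 = 0.095
- OR 3: 0.15/1.10 = 0.136
- OR 5: 0.25/1.20 = 0.208

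**Step 2, rejection region at p0 = 0.05.** The standard error is √[0.05 × 0.95 × (1/60 + 1/20,000)] = 0.0282. The critical value is √22.17 = 4.708. The threshold is 0.05 + 4.708 × 0.0282 = 0.183, or 10.96 of 60 alleles, so the SNP is called at 11 or more copies.

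**Step 3, probability of a call.** This is P(X ≥ 11) for X binomial with 60 trials and probability p1, and likewise with the matching threshold at other frequencies:

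| Population frequency | OR 2 | OR 3 | OR 5 | OR 10 |
|---|---|---|---|---|
| 1% | 0.7% | 3.2% | 16% | 65% |
| 5% | 2.5% | 19% | 73% | 99.8% |
| 20% | 4.0% | 42% | 96% | 100% |

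An exact binomial test in place of chi-squared would give 0.13%, 2.9% and 36% at 5% frequency for OR 2, 3 and 5. The size depends on the test, but the pattern does not: the risk is small for weak alleles and large for the moderate-to-strong effects that the section says it targets.

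**Step 4, do separate scans resolve it?** Suppose the same allele (5%, OR 5) is scanned independently in 30 Extreme and 30 Lack exomes of one disease. The chance that it is called in Extreme and missed in Lack is 0.73 × (1 − 0.73) = 0.20. It would then look specific to pain. Comparing two significance verdicts is not a test of the difference.

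**Step 5, a direct same-disease comparison.** For 30 versus 30 exomes, both groups with the same allele frequency (0.136 or 0.20), 2,000,000 simulated draws gave rejection rates of 0.048 and 0.050 at alpha 0.05, and below 1e-6 at alpha 2.5e-6. The disease-risk allele is then called at no more than about the nominal rate, provided it is unrelated to disease activity.

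**Step 6, the cost in power.** For a true pain allele at 30 versus 30 exomes:

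| Frequencies | alpha 0.05 | alpha 5e-5 | alpha 2.5e-6 | Exomes per group for 80% power at 2.5e-6 |
|---|---|---|---|---|
| 0.05 v 0.35 | 99% | 52% | 26% | 54 |
| 0.20 v 0.50 | 94% | 26% | 9% | 77 |

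Correcting only for the variants that pass the screen would put power somewhere between these columns. Even 30 per group is not assured: 12 listed phenotypes × 30 = 360, above the overall recruitment target of 350, which also includes Healthy Controls.

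**The case against.** **The work is exploratory.** All genetic analyses are labelled hypothesis-generating, the section promises effect sizes, confidence intervals and caveats, and individual results are not disclosed. This limits the weight of the point. The promised caveats, however, concern sample size and replication and do not address what a hit means.

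**The Lack cohort is already analysed.** A pure disease-risk allele would tend to be enriched in both cohorts, which is an indirect check, and the Aims plan a general comparison of high-pain and low-pain participants. That is true, but no between-cohort allele test is stated, and Step 4 shows how parallel scans can mislead. An article may leave the details of such a test to a fuller document. The general-population comparator, though, is stated here as the design.

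**The same-disease contrast is not clean either.** This objection stands. Under Methods and analysis the Extreme cohort is defined by high pain with low disease activity, and the Lack cohort by low pain with high disease activity. A severity allele with no effect on pain could differ between them. A reader might infer that an Extreme-versus-Lack difference proves a pain variant; the cohort definitions do not support that.

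**Table 1 may be only loose wording.** A reader might infer that the Lack cohort is barred from giving DNA. The documents do not support this. The Fig 1 legend, the Bio-sampling section and Key exploratory endpoint all include that cohort. The Remote mobile app section says that scores below 4 need not mean freedom from pain, so some Lack participants could meet even the Table 1 wording. Further genetic sampling criteria are in a supplement that is not shown. What remains is an internal contradiction.

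**Conclusion.** The point holds in a limited form. As written, the scan cannot separate alleles for disease from alleles for pain, contrary to its stated aim, and neither ancestry matching nor multiplicity correction changes that. Disease alleles *can* appear as pain alleles; it would be too strong to say that they will. At 30 exomes and 5% frequency the probability is 2.5%, 19% and 73% for OR 2, 3 and 5. These figures rest on the assumed 20,000 tests, 20,000 reference alleles and an allele with no effect on pain, and they are lower with an exact test. Because the analysis is exploratory, this is a change that should be made rather than a fault that undermines the study's primary result. The Table 1 wording is a separate inconsistency.

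**What to change.** 1. Keep the population scan as a screen.
2. For polycystic kidney disease, inflammatory bowel disease and chronic pancreatitis, add a direct Extreme-versus-Lack allele comparison of the screened variants, stratified by disease. Report effect sizes and confidence intervals as supporting evidence and not as a condition that every variant must pass.
3. State two limits of that comparison: power is low at about 30 versus 30, and the cohorts differ by design in disease activity. Add a sensitivity analysis using the disease activity scores already collected in the structured clinical interview.
4. Label as 'disease or pain' all population-scan hits without this support, and all hits in the three phenotypes with no same-disease Lack group.
5. Reconcile the bio-sampling row of Table 1 with the Fig 1 legend, the Bio-sampling section and Key exploratory endpoint, for example by giving it the app row's wording, which covers both pain and its absence.

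The cost is some wording and one added contrast on exomes already planned, and fewer variants will be presented as pain variants. Study status reports recruitment as ongoing and no analysis performed, so the change can still be pre-specified.

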### Structured clinical interview

Demographic information (age, race, sex at birth, self-identified gender) will be collected along with detailed medical history, including visceral disease diagnosis, family and menstrual history (for female at birth participants), history of surgeries, medications, and disease activity scores (see Supplementary Information for genetic sampling criteria).

The participants will also fill the following questionnaires:

1Brief Pain Inventory-Short-Form [21].2Body maps to indicate locations of pain (see Supplementary Information for examples) [22,23].3McGill Pain Questionnaire [24].4O’Leary-Sant Interstitial Cystitis Questionnaire (IC-Q) [25].5Pelvic Pain Urgency/Frequency Patient Symptom scale [26].6ACR 1990 Fibromyalgia Diagnostic Criteria [27].7ACR 2016 Fibromyalgia Diagnostic Criteria [28].8Malmo POTS Score (MAPS) [29].

Standard measurements, including weight, height, pulse, and blood pressure, will be taken [30].

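### Matching SNP controls only on ethnicity or country can let ancestry differences surface as exploratory pain leads; the study's own exomes allow closer matching

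*Protocol article*

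**What the plan says.** Under Key exploratory endpoint, the protocol article describes functional SNP allele discovery in exomes from people with visceral pain phenotypes. The aim is to "identify SNPs that occur at significantly different frequencies compared to the general population". The test is a "two-tailed chi-squared test with Bonferroni and false discovery rate corrections applied". On confounding it says: "Confounding variables will be minimized by matching subsets of control cohorts based on ethnicity or country".

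Four other statements bear on this.

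- **Who is recruited.** Table 1 asks for a diagnosis, age 18 or over, consent and residence in the UK. It sets no restriction on ancestry.
- **What is recorded.** Structured clinical interview: "Demographic information (age, race, sex at birth, self-identified gender) will be collected". Race is listed; ethnicity and country of origin are not.
- **Who gives samples.** The Bio-sampling section names only the two patient cohorts, and the list of first-visit assessments excludes healthy controls from sampling. The Fig 1 caption mentions optional sampling at the return visit, but the SNP comparison is in any case defined against the general population, so the comparator is external.
- **How many exomes.** "At least 30 exomes are required per visceral disease pain phenotype to yield statistically valid results". The genetic approaches are said to "have been proven effective in cohorts as small as 30–200 individuals with pain phenotypes".

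The section Primary endpoint analysis labels all genetic work exploratory.

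**The concern.** When cases are compared with outside reference frequencies, a SNP whose frequency varies with ancestry will differ if the two groups differ in ancestry mix, whether or not it has anything to do with pain. Matching is the right kind of remedy, but its quality depends on the variable used. Ethnicity labels can be coarse, and the word *or* lets country stand alone. For a UK-resident cohort, matching on country means matching to a UK reference, which leaves ancestry mix uncontrolled.

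The multiplicity corrections limit chance findings across many SNPs. They do nothing about a systematic difference, and that difference becomes easier to detect as the cohort grows.

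At stake is the list of candidate pain variants. The protocol promises to flag modest effects for replication, but a false hit from ancestry need not look modest (see the odds ratio in the working), so it could escape that flag.

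**Working it through.** **No figure of the plan to reproduce.** The protocol does not quantify this risk. Its 30-exome minimum comes without allele frequency, effect size, number of tests or power, so it cannot be re-derived. It is used here only as a cohort size.

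**Inputs**

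- From the protocol: n = 30 exomes per phenotype; two-sided chi-squared test with Bonferroni correction.
- Assumed: n = 100 as a larger comparison; 20,000 SNPs tested; a SNP at p0 = 2% in the reference and p1 = 20% (or 5%) in another ancestry; a share m = 5%, 10% or 20% of cases from that ancestry despite matching.

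**Threshold.** Alpha = 0.05/20,000 = 0.0000025, so z = 4.708. With 2n alleles and the reference frequency treated as known, the SNP is flagged when the case frequency exceeds p0 + z × sqrt(p0(1 − p0)/2n).

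- n = 30: 0.02 + 4.708 × sqrt(0.0196/60) = 0.105. Times 60 this is 6.3, so 7 alleles or more.
- n = 100: 0.02 + 4.708 × sqrt(0.0196/200) = 0.0666. Times 200 this is 13.3, so 14 alleles or more.
- An exact binomial test at the same alpha needs 10 and 17 alleles.

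**Chance of a false flag.** The case frequency is (1 − m) × p0 + m × p1. The table gives the binomial probability of reaching the threshold for p0 = 2%, p1 = 20%.

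| m | Case frequency | n = 30, chi-squared | n = 30, exact | n = 100, chi-squared | n = 100, exact |
|---|---|---|---|---|---|
| 0 | 2.0% | 0.02% | 0.00003% | 0.006% | 0.00007% |
| 5% | 2.9% | 0.17% | 0.0008% | 0.23% | 0.009% |
| 10% | 3.8% | 0.76% | 0.008% | 2.1% | 0.18% |
| 20% | 5.6% | 5.0% | 0.17% | 23.2% | 5.8% |

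With p1 = 5% and m = 20% the case frequency is 2.6%, and the chi-squared test flags it with probability 0.09% at n = 30 and 0.08% at n = 100.

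A finite reference of 20,000 alleles does not change the chi-squared results. Fixing the number of mismatched participants, instead of drawing alleles from the mixture, gives about 4% and 22% in place of 5.0% and 23.2%.

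**Sparse counts.** At n = 30 the expected count is 60 × 0.02 = 1.2 alleles, where the chi-squared approximation fails. Even with perfect matching its error rate of 0.02% is about 80 times the nominal 0.00025%. Most of the 5.0% therefore depends on the approximation; a test that holds its level gives 0.17%.

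**Apparent effect of a false hit.** At n = 30 the smallest flagged count is 7/60 = 11.7% against 2%, an odds ratio of (7/53)/(0.02/0.98) = 6.5. That is not modest.

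**Across all SNPs.** A second model inflates the chi-squared variance by lambda = 1 + 2nV, where V is the variance of the residual ancestry-driven frequency difference divided by p(1 − p). Expected false Bonferroni hits are 20,000 × 2 × Φ(−4.708/√lambda), which is 0.05 when V = 0. For assumed V of 0.001 and 0.01:

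- n = 30: lambda 1.06 and 1.60, or 0.10 and 4.0 false hits.
- n = 100: lambda 1.20 and 3.00, or 0.35 and 131 false hits.

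The result depends almost entirely on V, that is, on how close the matching is, and the protocol's wording does not fix that.

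**The case against.** The strongest reply is that the article is condensed. It does not say that ethnicity is self-reported, does not say that matching is the only safeguard, and leaves pipeline settings to a methods appendix. Ethnicity could mean a genetically defined group in a reference database. This stands in part: a reader might infer that the study has decided against using genetic ancestry, and the text does not show that. What it does fix is the matching variable, with country as a permitted substitute, and that is a stated choice open to criticism. If genetic groups are meant, one sentence saying so would settle most of the point.

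A second reply is that the larger figures assume matching has largely failed. This stands. No document supports a 10% or 20% mismatch or a tenfold frequency gap. With 5% mismatch, or with 2% against 5%, the chance is 0.2% or less at the sizes computed.

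A reader might also take the top of the cited range of 30 to 200 and conclude that a false flag is more likely than not: the same model gives 57% at n = 200 and 20% mismatch. The documents do not support this. That range describes earlier use of the approach, no single 200-exome comparison is stated, and the planned 350 participants are spread over three cohorts and many phenotypes.

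It would also be too strong to say that a chi-squared comparison cannot allow for ancestry. Stratified versions such as Cochran–Mantel–Haenszel exist, and matching is itself a form of control.

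Finally, the analysis is exploratory, with effect sizes, confidence intervals and STREGA reporting promised. So the harm is limited to false leads and does not reach the confirmatory result.

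**Conclusion.** The point holds in a limited form. As written, the SNP comparison may be protected against population structure by country alone, which does little for UK residents of unrestricted ancestry, and the multiplicity corrections do not fill the gap. Some exploratory hits may then reflect ancestry.

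In the assumed example the false-flag chance per affected SNP runs from about 0.1% to 5% at 30 exomes and from about 0.1% to 23% at 100. At 20% mismatch, sparse counts account for most of the upper figures: an exact test gives 0.17% and 5.8%. All of this rests on assumed frequencies, mismatch shares and number of SNPs. With close matching at 30 exomes the effect is small.

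The primary wearable analysis is untouched. The change is still worth making, because this is the protocol's key exploratory endpoint, the exomes are already planned ("Exome sequencing can detect most of these SNPs"), and Study status reports that no analysis has been done.

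**What to change.** Replace the ethnicity-or-country rule with the following.

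1. Infer each participant's genetic ancestry from the study exomes, for example by projecting principal components on a reference panel.
2. Compare each ancestry group with reference frequencies of the same group, using a stratified test or a reference weighted to the cohort's mix.
3. Use an exact test where expected allele counts are small.
4. Report the genomic inflation factor for each comparison.
5. Repeat the analysis without ancestry outliers and mark hits that disappear.

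If ethnicity already means a genetically inferred group, say so and drop country as an alternative.

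The cost is some extra bioinformatics and a need for ancestry-resolved reference frequencies; the documents do not say whether these are at hand. No new samples or participants are needed. Outlier removal shrinks the sample: losing 10% to 20% of 30 exomes leaves 27 to 24, below the protocol's own minimum. For that reason, outliers should stay in the stratified main analysis and be removed only in the sensitivity analysis.

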Missing data will be addressed using a complete-case analysis approach. No imputation methods will be applied for the wearable sensor data. Analyses will be restricted to participants with valid data for all variables included in the respective models. The extent and pattern of missingness will be reported descriptively. Where appropriate, we will perform sensitivity analyses to assess whether the exclusion of participants with missing data materially affects the results. For transparency, we will report the number of participants and observations included and excluded from each primary and sensitivity model in a CONSORT-style flow diagram and accompanying table. We will also present summary characteristics of participants with and without complete wearable data to allow readers to assess potential selection bias. This approach is justified by the observational nature of the study and the focus on real-world feasibility and data integrity.

This pre-specified analysis aligns with the SPIRIT recommendations for defining and justifying primary hypothesis-testing outcomes in clinical research protocols. All other objectives in this study, including genetic, immunological, and clustering analyses, are exploratory and will be pursued as hypothesis-generating efforts as more data becomes available.

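### Against a large population reference, the chi-squared test named for the exome SNP scan does not hold its Bonferroni or FDR error rate in groups of about 30 people, except for very common alleles

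*Protocol article*

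**What the plan says.** All of this is in the Protocol article, section Key exploratory endpoint, unless noted.

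- **Test:** SNPs with unusually high or low allele frequency "will be identified through a two-tailed chi-squared test with Bonferroni and false discovery rate corrections applied".
- **Comparison:** the aim is to find "SNPs that occur at significantly different frequencies compared to the general population". Confounding is to be reduced by "matching subsets of control cohorts based on ethnicity or country".
- **Group size:** "At least 30 exomes are required per visceral disease pain phenotype to yield statistically valid results". The same section adds that "The genetic approaches used have been proven effective in cohorts as small as 30–200 individuals with pain phenotypes".
- **Safeguards:** effect sizes, confidence intervals and sample-size limitations will be reported for all genetic findings. On replication, "Where modest effect sizes are detected, these will be flagged as requiring replication in larger cohorts".
- **Status:** under Primary endpoint analysis, the genetic and other non-primary objectives "are exploratory and will be pursued as hypothesis-generating efforts as more data becomes available".

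The article names no exact test, continuity correction or minimum expected count. It also does not give the number of SNPs tested, a lower limit on allele frequency, or the size of the reference.

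**The concern.** Thirty people carry 60 copies of each autosomal locus. An allele with population frequency below 5/60 = 8.3% therefore has an expected count under 5, the range in which the chi-squared approximation is usually distrusted. The approximation is poorest far out in the tail, and that is where a Bonferroni threshold sits. For an uncommon allele the count is strongly right-skewed, so a modest chance excess of a few alleles produces a very large chi-squared statistic.

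Bonferroni and FDR both take the p-values as given. If those are too small, neither procedure delivers the error rate it promises.

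At stake is which SNPs the scan reports for each phenotype, and where replication effort then goes. The planned replication flag gives little protection because it is tied to modest effects. Two alleles in 60 against a population frequency of 0.1% is (2/60)/0.001 = 33-fold enrichment, which nobody would call modest.

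**Working it through.** **The plan's own figure.** The minimum of 30 exomes is stated without effect size, significance level, number of tests or power, so it cannot be reproduced.

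**Inputs from the document.** n = 2 × 30 = 60 alleles at the minimum; 2 × 200 = 400 alleles at the top of the quoted range; two-tailed chi-squared test.

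**Assumed, because not stated.** Family-wise level 0.05; M = 20,000 tests, so the threshold is 0.05/20,000 = 2.5e-6, equivalent to a chi-squared statistic (1 df) of at least 22.17; reference either very large (frequency p treated as known) or of m alleles.

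**Step 1: one example.** Let p = 1% and suppose 5 of 60 alleles are seen. The expected count is 0.6.

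- Chi-squared: (5 − 0.6)² / (60 × 0.01 × 0.99) = 19.36/0.594 = 32.6, p = 1.1e-8.
- Exact binomial: p = 3.5e-4. Fisher's exact test against 1,200 of 120,000 reference alleles also gives 3.5e-4.

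The chi-squared p-value passes 2.5e-6. The exact one is more than two orders of magnitude away from it.

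**Step 2: actual size of the test, very large reference.** With X ~ Binomial(60, p), reject when (X − 60p)² / (60p(1 − p)) ≥ 22.17, and sum the binomial probabilities over that region.

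| p | expected count | smallest count declared significant | actual size | actual / 2.5e-6 |
|---|---|---|---|---|
| 0.1% | 0.06 | 2 | 1.70e-3 | 681 |
| 1% | 0.6 | 5 | 3.46e-4 | 138 |
| 5% | 3 | 11 | 1.72e-4 | 69 |
| 10% | 6 | 17 | 5.6e-5 | 22 |
| 20% | 12 | 27 | 1.05e-5 | 4.2 |
| 30% | 18 | 35 | 4.9e-6 | 2.0 |
| 40% | 24 | 42 | 2.7e-6 | 1.1 |

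**Step 3: larger groups.** With 400 alleles the ratio is 27 at 1%, 5.7 at 5%, 2.4 at 10% and 0.9 at 30%.

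**Step 4: number of tests.** At p = 5% with 60 alleles, the ratio is 15 for M = 1,000 and 360 for M = 500,000.

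**Step 5: finite reference.** This is the 2×2 Pearson test, 60 case alleles against m reference alleles, M = 20,000, with sampling of both groups.

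| m | ratio at p = 5% | ratio at p = 1% |
|---|---|---|
| 120,000 | 52 | 139 |
| 10,000 | 39 | 252 |
| 1,000 | 29 | 292 |
| 240 | 9 | 1.4 |
| 60 (1:1) | about 0 | about 0 |

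At 5% the excess falls steadily as the reference shrinks. At 1% it first rises and disappears only at a few hundred alleles. With equal groups the test is conservative.

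**Step 6: continuity correction.** Yates' correction, very large reference, leaves a ratio of 14 at 5% and 138 at 1%.

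**Step 7: expected false hits.** The intended number per phenotype is 0.05. If all 20,000 SNPs were null and frequencies followed an assumed 1/p spectrum up to 50%, the expected number is about 23 with a lower limit of 0.1%, 3.0 with 1%, 0.5 with 5% and 0.2 with 10%.

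**Step 8: exact test.** With the exact binomial test on 60 alleles and M = 20,000, the actual size is 0.01 to 0.97 times nominal at every frequency tried. Expected false hits under the spectra in step 7 are 0.02 to 0.03.

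**The case against.** The strongest objection is that the size of the problem rests on things the article does not state. Matching on ethnicity or country may give a much smaller comparator than a whole population database, and step 5 shows that a small enough one removes or reverses the inflation. A frequency floor of 5% or 10% would bring the expected false hits down to about 0.5 or 0.2. Thirty is a minimum, and larger groups do better. A condensed article may leave the reference size, filters and number of tests to a fuller document, so their absence is no fault.

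Most of this limits the size of the point without removing it. The test itself is named, and so is a comparison with the general population, which makes a large reference the likelier case. Inflation at 5% is still 29-fold with 1,000 reference alleles and about 6-fold with 200 people.

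It is also fair that the genetic work is exploratory and that limited power is conceded. That lowers the consequence. But the concession concerns missed effects, not spurious ones, and the replication flag covers only modest effects.

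A reader might go further and infer that most Bonferroni-significant SNPs would be false. The document does not support that. The share of hits that are false depends on how many true signals exist and how strong they are, and neither is given. Only an excess of expected false hits over the intended 0.05 can be shown.

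**Conclusion.** The point stands in limited form. With about 60 case alleles and a large reference, the named test does not keep the Bonferroni or FDR error rate for alleles below roughly 20–30% population frequency. The excess per SNP runs from about 4-fold at 20% to 138-fold at 1%, assuming 20,000 tests, a family-wise level of 0.05 and a very large reference. The figures move with the number of tests, the reference size and any frequency floor, and the direction reverses for a 1:1 control set. Because the analysis is hypothesis-generating and no confirmatory conclusion depends on it, this is something that should be fixed, not a threat to the study's main result.

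**What to change.** - Replace the chi-squared test with a two-sided Fisher's exact test on case versus matched-reference allele counts for every SNP. Use an exact binomial test only where the reference is large enough for its frequency to be treated as known; it is not a substitute for Fisher's test with a small matched subset.
- Apply the Bonferroni and FDR corrections to the exact p-values.
- Mark every significant SNP as needing replication, not only those with modest effects.
- When the analysis is specified in full, record the reference size, the number of SNPs in the test family and any frequency floor, so that the error rate can be checked.

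The cost is about one sentence and one line of code. Study status reports that no analysis has been done yet. The downside is that fewer SNPs will reach significance. Under the assumptions above, with a very large reference and the exact binomial test, the smallest significant count in 60 alleles rises from 5 to 7 at a population frequency of 1% and from 11 to 14 at 5%. The true case frequency needed for 80% power rises from about 0.11 to 0.15 and from about 0.22 to 0.27 respectively.
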